## Abstract

**Background:**

Despite the broad availability of antihypertensive drugs, approximately 40% of hypertensive patients fail to achieve the recommended blood pressure (BP) levels and may require alternative treatment(s). At present, renal denervation is the only proven non-pharmacological device-based alternative treatment available, but it is a costly, invasive, hospital-based procedure that is unlikely to be widely available. Transcutaneous autonomic neuromodulation (tAN)—if shown to be safe, acceptable, and efficacious—can offer a non-invasive, inexpensive, self-administered device-based innovative adjunct or alternative to pharmacological therapy.

**Methods:**

SCRATCH-HTN is a double-blind, sham-controlled trial, with 63 participants randomised on a 2:1 basis to receive either tAN or sham-tAN treatment. Hypertensive patients on medication were included if they had elevated systo-diastolic BPs on daytime ambulatory BP monitoring (ABPM) [systolic BP (SBP) of ≥135 and <170 mmHg and mean daytime diastolic BP (DBP) of ≥85 and <115 mmHg]. Participants were trained to self-administer tAN therapy for 30 min every day for first 14 days and then once a week for 10 weeks. The primary endpoint was change in daytime ambulatory SBP from baseline to 3 months. Secondary endpoints included change in 24-h ambulatory and office SBP and DBP, BP variability, heart rate variability, quality of life, and sleep quality from baseline to end of treatment. Other exploratory outcomes included evaluation of impact on functional exercise (6-min walk test), structural and functional changes in the heart, cognitive function, and central blood pressures. A subgroup of patients underwent detailed autonomic functional assessment at the start and end of the study.

**Conclusion:**

The SCRATCH-HTN trial is a phase 2a study testing the safety, acceptability, and potential efficacy of tAN treatment for improving blood pressure control in patients with elevated BP despite medication. It also explores the effects of tAN on sleep, exercise tolerance, heart rate variability, central BP, cardiac structure, and autonomic function. If effective, it could offer a transformative approach to hypertension management.

**Study Protocol Registration:**

Clinicaltrials.gov, identifier NCT05179343 and ISRCTN (14509154).

## Introduction

Hypertension or high blood pressure (BP) affects more than 1.3 billion people worldwide (1). It is the leading risk factor for premature death and disability and a key contributor to global disease burden (2–4). This is driven by its role as the leading global cause of cardiovascular and cerebrovascular disease mortality and morbidity, as well as its significant contribution to the global burden of chronic kidney disease (5–7). In England, one in three adults has hypertension, rising to over 60% amongst adults aged ≥65 years (8, 9). As such, the cost to healthcare systems is significant: Hypertension is estimated to cost the UK National Health Service (NHS) more than £2.1 bn annually (10).

Despite the widespread availability of antihypertensive drugs, 40% of all patients with hypertension fail to achieve the National Institute for Health and Care Excellence (NICE) recommended BP levels (<140 mmHg systolic and <90 mmHg diastolic) (9, 10). These patients are classified as having uncontrolled hypertension. Non-adherence to prescribed medications is a major challenge, partly due to drug intolerance/adverse side effects. The global prevalence of non-adherence to antihypertensive medication in diagnosed hypertensive patients is estimated to be around 27%–40% (11) and is present in approximately 84% of those with uncontrolled hypertension (12) and 37% of those with drug-resistant hypertension (11, 13). As such, there is an urgent, unmet clinical need for an effective therapy for uncontrolled and drug-resistant hypertension.

One possible therapy is device-based autonomic neuromodulation. During the development of hypertension, parasympathetic (vagal) activity declines, while sympathetic activation increases, which can, if left untreated, lead to chronically altered homeostatic autonomic imbalance. Redressing autonomic imbalance has already been achieved using catheter-based renal denervation (14, 15), which appears to be a safe treatment for reducing arterial blood pressure (14, 16). A recent meta-analysis found modest but significant reductions in 24-h ambulatory systolic BP (SBP, mean reduction = −2.23 mmHg) and 24-h ambulatory diastolic BP (DBP, mean reduction = −1.16 mmHg) following renal denervation amongst uncontrolled hypertensive patients on antihypertensive medication (17). However, renal denervation is an invasive procedure, requiring hospitalisation and tertiary care delivered by experts (15). This limits universal adoption, while uncertainty remains regarding the duration of the blood pressure-lowering effect and the requirement for repeat procedures.

Autonomic balance can potentially be reinstated non-invasively using a method called transcutaneous autonomic neuromodulation (tAN), otherwise known as transcutaneous vagus nerve stimulation (tVNS) (18). In this method, electrical stimulation is applied to the regions of the outer ear that are innervated by sensory (afferent) fibres of several cranial and spinal nerves, including the auricular branch of the vagus nerve (18, 19). These afferent nerve fibres, constituting 80% of the vagus nerve, transmit sensory information, predominantly from visceral organs, to the nucleus tractus solitarius (NTS) where 95% of vagal afferent fibres terminate. Efferent vagal nerve fibres leaving the NTS via the dorsal vagal nucleus and nucleus ambiguous have various visceral organ targets and influence an array of homeostatic physiological functions including BP. The firing of efferent vagal nerve fibres reduces BP through a range of targets and mechanisms, including cardiovagal innervation of the heart, which produces negative inotropic and chronotropic effects, and attenuation of sympathetic activity (via inhibition of the rostroventrolateral medulla) that reduces vasoconstriction and the activity of the renin–angiotensin–aldosterone system (20–22). Recruitment of these afferent projections through transcutaneous electrical stimulation of the auricular nerve modulates the autonomic control circuits in the brainstem and acutely shifts the autonomic balance towards a net vagal dominance (23–26), as assessed by baroreflex sensitivity (27) and heart rate variability measures (19, 23, 28). These effects are consistent with vagal recruitment and sympathetic inhibition as demonstrated by beneficial effects of tAN in patients with epilepsy (29, 30), coronary artery disease (31), and atrial fibrillation (32, 33).

Recent evidence suggests that autonomic neuromodulation via unilateral tAN applied daily for 3 months reduced BP in untreated young individuals with grade-1 hypertension (34). The study was open-labelled, unblinded, and BP was measured by patients at home with significant self-reported reductions reported after 1 month. These data, however, are at odds with the results of the study by Stavrakis et al. (35) who used an identical device and treatment protocol involving unilateral daily tAN and observed no change in office BP in patients with heart failure with preserved ejection fraction; 96% of these patients were hypertensive. Most published studies, including the two referenced, that involved longer periods of tAN employed unilateral auricular stimulations, were open-labelled, and used inconsistent methods of BP monitoring, potentially leading to ascertainment bias.

The SCRATCH-HTN study (Sham-Controlled Randomised Trial Evaluating the Safety, Acceptability, and Efficacy of Autonomic Neuromodulation using Transcutaneous Vagal Sensory Stimulation in Uncontrolled Hypertensive Patients) tests the hypothesis that tAN treatment is safe and acceptable, improves the control of BP in hypertension, and improves wellbeing amongst those receiving the active treatment compared to those on sham treatment. In this study, tAN is applied to both ears (bilaterally) using a modified and improved protocol. This stimulation protocol was developed based on significant evidence indicating that applying sensory stimuli bilaterally is more effective than unilateral stimulation in inducing brain plasticity and neuromodulation (36, 37). Using this protocol in our unpublished proof-of-concept study of 10 patients with drug-resistant hypertension, bilateral tAN reduced 24-h SBP by an average of 14 mmHg at 1 month after the course of tAN compared to before the treatment (Supplementary Figure 1). This set the premise for the current trial protocol, although the findings require critical interpretation given the observational, single-arm design of the proof-of-concept study conducted in a small number of self-selected individuals. Further details on the study background and trial design rationale can be found in the clinical investigational plan (Supplementary Material 4).

The data obtained will be used to develop larger efficacy and cost-effectiveness follow-up studies. The SCRATCH-HTN trial also includes a sub-study of participants to evaluate autonomic function at baseline and at the end of the treatment period. This will provide mechanistic insights into the effects of treatment on components of the autonomic nervous system responses. The present manuscript outlines the protocol for this trial.

## Methods and analysis

### Patient and public involvement

During study development and prior to the start of the trial, a group of hypertensive patients were invited to provide feedback. Patient and public involvement representatives also served on our trial steering committee, contributing to the study design, device logbooks, and questionnaires, and overseeing the conduct of the study.

### Trial design

The SCRATCH-HTN trial is a double-blind, sham-controlled study, with block randomised on a 2:1 basis, where participants receive either tAN or sham-tAN treatment. tAN was applied using the AffeX-CT electronic device developed by Afferent Medical Solutions, Ltd (UK).

### Study population

Study participants were recruited from six participants-identifying centres (PICs) in and around London (Supplementary Table 1). For consistency, all participants were processed at a single site: the William Harvey Clinical Research Centre, Queen Mary University of London. Hypertensive patients, who were receiving between one and four antihypertensive medications, were eligible for recruitment if they had elevated systo-diastolic BP on daytime ambulatory BP monitoring ((ABPM): daytime average SBP of ≥135 and <170 mmHg, and daytime average DBP of ≥85 and <115 mmHg) and the presence of one or more of the following conditions: obesity, type 2 diabetes, heart rate ≥70 beats per minute, metabolic syndrome, dyslipidaemia, or polycystic ovarian syndrome (see Table 1 for summary of key inclusion criteria and further details in Supplementary Table 2). Exclusion criteria included atrial fibrillation, eGFR < 45 mL/min, type 1 diabetes mellitus, poorly controlled type 2 diabetes (HbA1c > 69 mmol/mol) and/or or insulin therapy, and orthostatic hypotension (defined as a fall >20 mmHg in SBP on moving from sitting to standing). The full list of exclusion criteria can be found in Supplementary Table 3.

**Table 1 T1:** Summary of participant inclusion criteria.

Inclusion criteria
Aged ≥18 and <80 years
Taking between 1 and 4 antihypertensive medications (inclusive)
Confirmed diagnosis of hypertension
24-hour ABPM mean daytime^a^ SBP ≥ 135 mmHg and <170 mmHg and mean daytime DBP ≥85 and <115 mmHg
Moreover, participant must have **one or more** of the following associated conditions:
Obesity [Body Mass Index (BMI) > 30 kg/m^2^ or waist circumference >94 cm (men) or >80 cm (women)] NB. For participants of Southeast Asian/Chinese/Japanese origin these cut-offs are >90 cm (men) or >80 cm (women)
Type 2 diabetes-controlled or sub-optimally controlled (HbA1c ≤ 8.5% or ≤69 mmol/mol) on diet and/or medications except insulin
Heart rate (any one of the three recordings) ≥70 bpm (measurement taken after 5 min of rest in a seated position) or heart rate ≥60 bpm if taking beta-blocker medication
HbA1c ≥ 42 mmol/mol or fasting glucose (if available) ≥5.6 mmol/L **AND** either low HDL cholesterol (≤1.03 mmol/L for men and ≤1.29 mmol/L for women) or high triglycerides (≥1.7 mmol/L)
Both low HDL cholesterol (≤1.03 mmol/L for men and ≤1.29 mmol/L for women) **AND** high triglycerides (≥1.7 mmol/L)
Diagnosed or known polycystic ovarian syndrome

Full inclusion and exclusion criteria detailed in Supplementary Tables S1, S2.

^a^
Daytime defined as hours from 0700 to 2300.

### Randomisation

Eligible participants were randomised in a 2:1 ratio to the tAN and sham-tAN intervention arms, respectively, using the online randomisation tool “Sealed Envelope.” This tool employed block randomisation and a dynamic minimisation approach to ensure balanced allocation between treatment groups (38). The minimisation algorithm incorporated the following baseline factors: age (<65 or ≥65 years), sex, body mass index (BMI; <30 or ≥30 kg/m^2^), and mean daytime average SBP (<160 or ≥160 mmHg).

### Description of intervention

All randomised participants were provided with identical devices, with allocation to either the tAN or sham-tAN arm concealed. On the day of randomisation, all participants received standardised training using a dedicated training device before being assigned their personal study device. Each participant was provided with an individually set stimulation threshold as well as access to further training resources via a user guide (see Supplementary Material 2—User Guide), demonstration video, and telephone support.

During device training, participants were instructed to place the electrode clips (with electrode surfaces made of electrically conductive rubber) on the left and right tragi (Figure 1). The current amplitude was gradually increased by the trainer, starting from 0.1 mA, until the participant felt a tingling sensation, after which it was reduced to set the level of stimulation at ∼1.5 mA below this threshold (Figure 1). Once the threshold current was determined, participants were issued their individual units, which were identical to the training device but with concealed controls. Stimulation current was set to 0 mA (sham-tAN) or ∼1.5 mA below the individual perception threshold (tAN), with 200 *μ*s pulses generated at a frequency of 30 Hz.

**Figure 1 F1:**
[figure not shown]
AffeX-CT device settings. The individual sensitivities of the auricular tragi regions to tAN stimulation were determined during the randomisation visit using a dedicated training device. During device training, participants were instructed to place the electrode clips on the left and right tragi. The current amplitude was gradually increased by the investigator conducting the training, starting from 0.1 mA, until the participant felt a tingling sensation. The current was then reduced to set the level of stimulation at ∼1.5 mA below this threshold. Once this threshold current was determined, participants were issued their personal device units, identical to the training device but with concealed controls. The stimulation current was set to 0 mA (**a**; sham-tAN) or ∼1.5 mA below the individual perception threshold (**b**; tAN), with 200 *μ*s pulses generated at a frequency of 30 Hz.

Participants were instructed to use the device independently at home, ideally setting aside 30 min in the evening when relaxed and not engaging in strenuous activity. Light activities such as reading or watching TV were recommended during stimulation. Before using the device, participants cleaned the outer ear. The device's two ear clip leads (left and right) were moistened with a wet tissue at the contact points and attached to the left and right tragi. The device was then activated to stimulate the auricular branch of the vagus nerve.

For participants in the sham-tAN arm, the same training procedure was followed. However, the sham AffeX-CT device was programmed to deliver no stimulation current to the tragus. Otherwise, the sham device was identical in all other aspects. The participants, clinical research team, and data analysis team were all blinded to the intervention.

### Procedure

Trial participants were required to attend five visits spanning 12 weeks/84 days: visit 1 for the screening; visit 2 for baseline and randomisation at Day 0; visit 3 at Day 14; visit 4 at Day 28; and visit 5 for the end of treatment at Day 84 (see Figure 2 for Flowchart). Participants also received several telephone calls: one between days 1 and 3, one on Day 7, one at Day 56, and one at Day 112 (post-trial follow-up). Participants received text and/or email reminders at Day 42 and Day 70. The expected total duration of participation was 16 weeks. No changes in antihypertensive medications were permitted during the trial (between randomisation on Day 0/visit 2 and end of treatment on Day 84/visit 5). Table 2 summarises the assessments and data collected at each visit with a full detailed schedule provided in Supplementary Table 4.

**Figure 2 F2:**
[figure not shown]
Flowchart for SCRATCH-HTN main trial.

**Table 2 T2:** Summary schedule of assessments and timeline of data collected.

Schedule	Visit 1 (Screening Visit)	Visit 2 (Baseline/Randomisation Visit)	Phone Call 1	Phone Call 2	Visit 3	Visit 4	Text/Email Reminder1	Phone Call 3	Text/Email Reminder2	Visit 5 (End of treatment visit)	Phone Call 4 Follow-up
Timeline (weeks/days)	n/a	Week 0 Day 0	Day 1-4	Week 1 Day 7	Week 2 Day 14	Week 4 Day 28	Week 6 Day 42	Week 8 Day 56	Week 10 Day 70	Week 12 Day 84	Week 16 Day 112
Visit window	28 days (−1 day)	n/a	n/a	±3 days	±5 days	±5 days	±3 days	±3 days	±3 days	±5 days	±3 days
Informed consent medical, demographic and social history Inclusion & Exclusion criteria reviewed	X										
Vital signs	X^a^	X			X	X				X	
Weight & BMI	X^b^	X								X	
Review of concomitant medication(s) and AE	X	X	X	X	X	X		X		X	X
24-hour ABPM	X	X^c^				X				X	
Office BP	X	X^d^			X	X				X^d^	
24-hour Holter ECG		X				X				X	
6-minute walk test (6 MWT)		X			X	X				X	
Echocardiogram		X								X	
Electrocardiogram (ECG)	X										
Blood test^e^	X	X				X				X	
Urine sample^f^		X				X				X	
Device procedure and logbook reviewed		X	X	X	X	X	X	X	X	X	
Extent of adherence scales questionnaire		X			X					X	
Insomnia severity index (ISI) Questionnaire		X				X				X	
Blinding and AffeX-CT device usability questionnaire						X				X	
EQ-5D QoL questionnaire^g^ cognitive assessment		X			X	X				X	

^a^
X Height and waist circumference collected at visit 1.

^b^
Vital signs Pulse rate, respiratory rate, temperature, and oxygen saturation assessments.

^c^
X Screening 24-h ABPM will be used at baseline, only if within screening period and no subsequent treatment changes have been made. Otherwise, 24-h ABPM must be repeated at baseline (randomisation) visit.

^d^
X Central BPs will also be taken at visits 2 and 5.

^e^
Blood Test Full blood count (FBC), lipid profile, glucose (fasting), HbA1c, fructosamine, U&Es, Serum pregnancy for female participants on screening and randomisation visits. Blood samples for storage and later evaluations (plasma and serum) will also be taken at visits 2, 4, and 5.

^f^
Urine Sample Urinary albumin creatinine ratio and urinary antihypertensive drug screen. Urine pregnancy test for women <55 years age at visits 1 and 2.

g X EQ-5D QoL Questionnaire also completed at week 16, Phone Call 4 Follow-up.

A maximum of 28 days was allowed between screening and randomisation. At the screening visit (visit 1), all participants provided informed signed consent to enrol into the study, along with demographic information, medical and social history, and current concomitant medications. Vital signs, height and waist circumference, weight and BMI, ECG, 24-h ABPM, and office BP assessments were collected. Blood samples were taken from all participants, and for female participants <55 years of age, serum and urine pregnancy testing was completed. Inclusion and exclusion criteria were evaluated during the screening period. At the chief investigator's (CI) discretion, the screening visit could be repeated once. Only after all screening assessments were completed, and once the participant was eligible and consented to the trial, were they invited to attend the baseline/randomisation visit (visit 2).

At baseline and randomisation (visit 2, Day 0), participants were trained to use the device and provided with their personal AffeX-CT devices (including a user manual, see Supplementary Material 2—User Guide), device logbook (to record the date, time, and duration of each stimulation session and the presence of any adverse effects), and participant ID card. Patients also underwent the following assessments: vital signs, weight and BMI, 24-h ABPM, office BP, central BP, 24-h Holter ECG, 6-min walk test (6 MWT), echocardiogram, blood tests (for pathology assessment and for storage and later evaluations), and urine tests (for urinary albumin–creatinine ratio and urinary antihypertensive drug screening to objectively assess adherence to medications).The trial participants were trained on using the device, prescribed an individualised stimulation intensity as described earlier, issued their assigned randomised device, and asked to perform the first self-stimulation under the direct supervision of the clinical research staff. Participants had their safety BPs recorded after 30 min of their first self-stimulation. Participant also completed three questionnaires [Extent of Adherence scale (39), Insomnia Severity Index (ISI) (40), and EuroQol Five-Dimensional scale for Quality of Life (EQ-5D QoL)] (41) and a cognitive assessment (PEBL 2.0) (42).

Participants self-administered the treatment using the device for 14 consecutive days, 30 min each evening. During this period, participants received two phone calls as reminders to apply treatment daily for the duration of the initial course of treatment and complete device procedure and device logbook entries. Concomitant medication and adverse events (AEs) were simultaneously reviewed.

After 14 days, visit 3 was conducted where medications, logbooks, and AEs were reviewed. The participants also underwent office BP measurement, vital sign assessment, and 6 MWT and completed the cognitive assessment, adherence, and QoL questionnaires. Participants were then asked to self-administer therapy once a week for a further 10 weeks.

Visit 4 took place on Day 28. At this visit, vital signs, 24-h ABPM, office BP, 24-h Holter ECG, and 6 MWT were assessed, and a review of concomitant medication(s), use of the device, logbook, and AEs was completed. Participants had their blood and urine samples collected for safety and medication adherence assessments and also completed cognitive assessment and questionnaires on device usability, QoL, insomnia, and blinding. Email/text reminders to complete the device procedure and logbook entry were sent at Day 42. A phone call was conducted at Day 56 reminding participants to continue using the device and completing logbook entries, while concomitant medication(s) and AEs were reviewed. Another email/text reminder was sent on Day 70.

The end-of-treatment visit (visit 5) took place at the end of week 12 (Day 84). Participants completed the following assessments: vital signs, weight and BMI, 24-h ABPM, office BP, central BP, 24-h Holter ECG, 6 MWT, echocardiogram, and safety blood and urine samples. Concomitant medication(s), device logbooks, and AEs were reviewed, and the device was returned. Participants then completed all trial questionnaires and the final cognitive assessment.

After the trial, follow-up was conducted at week 16 (Day 112) with a phone call to review concomitant medication(s), AEs, and the QoL remotely.

In addition, an extra visit/clinical assessment was offered as per each participant's clinical requirement, particularly for those with either high (SBP > 180 mmHg) or low (SBP < 100 mmHg) BP, symptomatic postural hypotension, or other clinical concerns.

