### Statistical methods

Baseline demographic and physiological characteristics will be presented separately by trial group. The main analyses of the primary and secondary endpoints will be conducted on an intention-to-treat population (all randomised participants with available data irrespective of their compliance with the device) and on a per-protocol population (all participants with treatment compliance on 80% or more days during the trial). Any participants who required a change in antihypertensive medication during the treatment period for safety/ethical reasons or otherwise will be included in the intention-to-treat analyses but not in the per-protocol analyses.

The primary endpoint, change in daytime ambulatory SBP, will be calculated for each participant by subtracting the end-of-treatment measurement (at 3 months) from the baseline measurement. The mean change in daytime SBP within each group will be presented with 95% confidence intervals (CIs) within the active treatment arm. The crude difference in the mean change in daytime SBP between treatment arms will be calculated with a 95% CI, and a two-sample *t*-test with equal variances will be used to test the null hypothesis of no difference in the change in SBP between groups.

Adjusted analyses will be conducted using linear regression, comparing change in SBP between treatment groups while adjusting for baseline daytime ABPM SBP (ANCOVA), age, sex, and BMI. The estimated adjusted difference in change in SBP will be presented, along with 95% CIs and *p*-values. The primary endpoint will also be analysed according to subgroups defined by (i) BMI at baseline (<30 kg/m^2^ vs. ≥30 kg/m^2^), (ii) diabetes status at baseline, (iii) age at baseline (<65 years vs. ≥65 years), and (iv) mean ABPM daytime SBP at baseline (<160 mmHg vs. ≥160 mmHg); for each of these four risk factors, a test for interaction will be conducted between groups. Moreover, data from the urinary antihypertensive drug screening samples collected at visits 2, 4, and 5, providing objective longitudinal data on antihypertensive medication adherence for each participant from the point of randomisation to end of treatment, will be used to adjust the analysis of the primary outcome for partial or non-compliance to medications.

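### The ABPM that qualifies a patient is by default the baseline of the primary endpoint, so the active-arm change includes regression to the mean, and the article disagrees with itself on whether a visit-2 ABPM exists

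*Protocol article*

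**What the plan says.** All references are to the protocol article.

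- **Entry (Study population).** Patients need a "daytime average SBP of ≥135 and <170 mmHg, and daytime average DBP of ≥85 and <115 mmHg".
- **Baseline rule (Table 2, footnote c, attached to the visit-2 ABPM cell).** "Screening 24-h ABPM will be used at baseline, only if within screening period and no subsequent treatment changes have been made". The alternative follows at once: "Otherwise, 24-h ABPM must be repeated at baseline (randomisation) visit". The Procedure section allows at most 28 days between screening and randomisation.
- **Visit 2 as narrated (Procedure).** "Patients also underwent the following assessments: vital signs, weight and BMI, 24-h ABPM, office BP, central BP", with no condition attached. At the same visit participants were "asked to perform the first self-stimulation under the direct supervision of the clinical research staff". The text does not say whether an ABPM at that visit came before the stimulation.
- **Rescreening (Procedure).** At the chief investigator's discretion "the screening visit could be repeated once". No reasons are given.
- **Sizing (Sample size).** The trial is powered on the change in daytime SBP within the active arm, by a paired t-test (mean change 5.5, SD 11 mmHg, n = 34, inflated to 42).
- **Analysis (Statistical methods).** Mean changes "will be presented with 95% confidence intervals (CIs) within the active treatment arm". The crude arm comparison is a two-sample t-test on change. The adjusted comparison is a regression on baseline daytime SBP, age, sex and BMI.

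**The concern.** A reading chosen because it is high tends to be followed by a lower one, even if nothing has been done to the patient. Here the chosen reading and the starting point of the primary endpoint are, by default, the same daytime SBP average. With an inert device the active arm would still be expected to show a fall, and the 95% CI around that fall would be centred on the wrong value.

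This matters more than in most sham-controlled trials because the sample size rests on that single-arm change. The Discussion also sets the hoped-for SBP reduction beside renal denervation and single drugs, so an uncontrolled fall is easily read as a device effect.

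The remedy depends on whether a second pre-treatment recording exists. Footnote c implies that in the ordinary case it does not; the visit-2 narrative implies that it does.

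**Working it through.** **1. The plan's own figures reproduce.**
- Paired t-test, 5.5 mmHg, SD 11, two-sided 0.05: power is 79.5% at n = 33 and 80.8% at n = 34. Inflation: 34 / 0.9 / 0.9 = 41.98, so 42.
- Two-sample t-test, SD 11, 80% power: the detectable difference is 8.37 mmHg at 42:21 and 9.34 mmHg at 34:17. The article gives 8.4 and 9.3.

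**2. Assumptions that are not in the article.** Source population with mean daytime SBP 135 to 150 mmHg and between-person SD 10 to 13. If the whole change SD of 11 is recording-to-recording noise, the within-person SD is w = 11/√2 = 7.8; if half of that variance is, w = √(121/4) = 5.5. For the DBP criterion: mean 82 to 90, between-person SD 8, within-person SD 0.65w, correlation with SBP 0.6 for true levels and 0.7 for errors. No device effect.

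**3. Size of the shift, SBP criterion only.** With between-person SD b and s = √(b² + w²),

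shift = (w²/s) × [φ(a₁) − φ(a₂)] / [Φ(a₂) − Φ(a₁)], where a₁ = (135 − μ)/s and a₂ = (170 − μ)/s.

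For μ = 142, b = 12, w = 7.8: s = 14.31, a₁ = −0.489, a₂ = 1.956, so the shift is 4.25 × 0.295/0.662 = 1.9 mmHg. Over the assumed range this version gives 0.2 to 3.8 mmHg.

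**4. Size of the shift, SBP and DBP criteria together (simulation, 3 million source patients per setting).** The table shows the largest and smallest shift for each w. The last column is how often the active-arm 95% CI (n = 42, change SD 11) would exclude zero with no device effect; it should be 5%.

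| w | mean SBP | between-person SD | mean DBP | shift (mmHg) | CI excludes 0 |
|---|---|---|---|---|---|
| 7.8 | 135 | 10 | 82 | 4.4 | 72% |
| 7.8 | 150 | 13 | 90 | 1.0 | 9% |
| 5.5 | 135 | 10 | 82 | 2.5 | 30% |
| 5.5 | 150 | 13 | 90 | 0.6 | 6% |

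As a share of the planned 5.5 mmHg: 0.6/5.5 = 11% and 4.4/5.5 = 80%.

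**5. Effect of the choice of baseline.** With an unselected visit-2 recording alone, the shift is 0.0. With the mean of the two recordings it is halved (for example 4.4 to 2.2).

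**6. The randomised comparison.** In 20,000 simulated trials at the step 3 setting, with no device effect, the tAN-sham difference averaged 0.00 mmHg and the two-sample t-test rejected in 4.8%. The within-arm test at n = 42 rejected in 21%.

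**7. Precision if everyone has both recordings.** Averaging two baselines removes w²/2 from the variance of the change.
- w² = 60.5: √(121 − 30.25) = 9.53; detectable difference at 42:21 falls from 8.4 to 7.2 mmHg.
- w² = 30.25: √(121 − 15.1) = 10.29; it falls to 7.8 mmHg.
- ANCOVA residual SD at the step 3 setting: 10.2 with the screening recording, 9.8 with visit 2 alone, 9.3 with the mean of both.

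Replacing the screening recording by visit 2 alone removes the shift but does not reduce the change SD (11.0 against 10.5 in the selected sample).

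**The case against.** The strongest reply is that the only hypothesis test specified for the main effect is tAN against sham. Both arms regress equally in expectation, so neither that test nor the ANCOVA is biased; step 6 confirms this. The within-arm change receives only a CI, and the Sample size section already says the sham arm is there to account for Hawthorne and placebo effects. This stands as far as the randomised comparison goes. It does not rescue the within-arm estimate, which is planned, reported with an interval and used to size the trial.

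A reader might infer more than the article supports:

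- **That a visit-2 recording exists and is discarded.** The Table 2 cell carries footnote c, and the narrative may simply be listing that column. The natural reading of the footnote is that no second recording is made in the ordinary case. When the footnote itself calls for a repeat, the new recording is the one used. The firm point is the disagreement between the two statements.
- **That every change from baseline is affected.** The rule is conditional, and office BP, Holter, sleep and quality-of-life endpoints do not use this recording.
- **That rescreening makes the shift worse.** This would hold if patients below the window were given a second chance. No reason for repeats is given; a lapsed screening period, or a first reading above the window, would fit equally well.
- **That a visit-2 recording is automatically a clean baseline.** A 24-h recording started at that visit may run into the first supervised stimulation.

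The size is also open to challenge. It rests on assumed populations, and the 72% figure is an extreme corner of the range.

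**Conclusion.** The concern holds for the within-arm change in daytime SBP among participants whose qualifying ABPM serves as baseline. By footnote c that is the default. The apparent fall is overstated by about 0.6 to 4.4 mmHg under the assumed populations, or by 0.2 to 3.8 mmHg if only the SBP criterion is modelled. The direction is the same throughout those ranges; the size depends on the source population and on how much of the SD of 11 is recording-to-recording noise, neither of which the article gives.

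The article does not support the conclusion that the trial's randomised result is biased. What the between-arm analysis could gain is precision, and only if second recordings exist and are used together with the first. Separately, footnote c and the visit-2 narrative must be reconciled. This is worth correcting, but it does not threaten the tAN-sham comparison.

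**What to change.** Before unblinding:

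1. Reconcile footnote c with the visit-2 narrative. State how many participants have a visit-2 ABPM, whether it was completed before the first stimulation, and which recording is the baseline.
2. For the **within-arm change**, where a valid visit-2 ABPM under unchanged medication was completed before the first stimulation, start from that recording and not from the qualifying one. A mean of the two would keep half the shift.
3. For the **between-arm change and the ANCOVA covariate**, use the mean of all valid pre-stimulation recordings made under the same medication. Leave out any recording that precedes a treatment change.
4. Where only the qualifying recording exists, report the within-arm change as including regression to the mean, and rest any efficacy conclusion on the tAN-sham difference. Do not estimate a correction from the few participants who happen to have two recordings if they were rescreened or changed treatment; they would not represent the rest.

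The cost is a baseline definition in the analysis plan, applied to recordings already made; recruitment is complete, so no new ones can be added. The reported within-arm fall will probably be smaller, and the number of baseline recordings will vary between participants. If few second recordings qualify, the precision gain is correspondingly small and step 4 carries most of the correction.
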